**3. AIM OF STUDY**

The main aim of the trial is to intervene in with photobiomodulation, delivered via LED, to determine the efficacy of using this modality to treat the symptoms of Parkinson’s disease and determine if symptoms of Parkinson’s disease are able to be modified to improve quality of life outcomes.

**4. OBJECTIVES**

1. to determine the effect of PBMt over a 12-week period on a variety of fine and course motor symptoms
2. to determine the effect of PBMt over a 12-week period, on a cognitive function, including social cognition
3. to determine the effect of PBMt over a 12-week period, on the composition of the intestinal and oral microbiome

**5. HYPOTHESIS**

5a. Primary Hypothesis: PBMt will have no adverse effects on PD participants

5b. Secondary Hypothesis: PBMt will reduce the symptoms of PD

5c. Tertiary Hypotheses: PBMt will alter the microbiome

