**11. STUDY OUTCOMES**

**10a. Primary Outcome:** Improved quality of life

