**10b. Secondary Outcomes:**

- Course motor control (up-and-go test; timed walk; step test)
- Fine motor control (spiral test; 9-hole peg test; writing task)
- Balance (static; tandem)
- Cognition (Montreal Cognitive Assessment)
- Self-assessment (PDQ39 questionnaire; PDSS sleep scale)
- Carer diary of daily living
- Smell identification test
- Microbiome analysis

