**12b. Measurement tools used**

- Demographic data
- Physiognomic measurement (height and weight)
- Step test (Appendix 2)
- 10 meter walk test (Appendix 2)
- Spiral test (Appendix 2)
- Montreal Cognitive Assessment (MoCA) test (Appendix 3)
- Timed up-and-go (TUG) (Appendix 2)
- 9-hole peg board (Appendix 2)
- Static balance (feet apart, feet together, eyes open, eyes closed) (Appendix 2)
- Tandem balance (eyes open, eyes closed) (Appendix 2)
- Hand-writing assessment
- PDQ-39 questionnaire (Appendix 4)
- Parkinson’s disease sleep scale (PDSS) questionnaire (Appendix 5)
- Social cognition questionnaires (Appendix 6)
- Carer diary of daily activities (Appendix 7)
- Microbiome analysis (faecal and saliva sample)
- Heart rate variability
- Smell Identification test

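### The primary hypothesis is about safety but no adverse-event data are planned, while the primary outcome, quality of life, has no named instrument and PDQ-39 is listed as secondary

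*Protocol*

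**What the plan says.** The protocol states its main question in four places.

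- Section 3 (Aim) sets out "to determine the efficacy of using this modality to treat the symptoms of Parkinson’s disease", and the same sentence goes on to name quality of life as what is to be improved. Safety is not mentioned.
- Section 4 (Objectives) lists three items: motor symptoms ("to determine the effect of PBMt over a 12-week period on a variety of fine and course motor symptoms"), cognition and the microbiome. Neither quality of life nor safety is among them.
- Section 5 (Hypothesis) gives 5a as "Primary Hypothesis: PBMt will have no adverse effects on PD participants" and 5b as "Secondary Hypothesis: PBMt will reduce the symptoms of PD"; 5c concerns the microbiome.
- Section 11, item 10a gives the primary outcome as "Improved quality of life" and nothing more.

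PDQ-39 appears in Section 11, item 10b, among the secondary outcomes, under "Self-assessment (PDQ39 questionnaire; PDSS sleep scale". It appears again in the tool list of Section 12b as "PDQ-39 questionnaire (Appendix 4". Section 12c, on safety, relies on earlier research and on the Brisbane and Adelaide studies; it sets no collection, definition or analysis of adverse events. Section 13b applies the same descriptive and half-SD approach to every outcome measure and singles none out as primary.

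**The concern.** A primary hypothesis should point to a primary outcome, and that outcome to a measurement. Here the chain breaks twice. The hypothesis is about harm, but harm is not measured. The outcome is quality of life, but no hypothesis or objective addresses it and no scale is attached to it.

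Two things are at stake. First, the trial could finish with nothing systematic to say on the hypothesis it ranks first. Events that nobody asked about cannot be recovered reliably afterwards, and the gap widens if treatment moves to participants' homes under Appendix 8, without a researcher directing the sessions. Second, with no designated score, time point or contrast for quality of life, the primary result would have to be settled after the protocol is fixed.

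**Working it through.** The protocol gives no significance level, power, effect size or SD behind its 20 per group, so there is no stated figure to reproduce. The main check is a cross-reading; the arithmetic shows what 20 participants can support.

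**1. Is there any data source for hypothesis 5a?**
- Section 11 (10a and 10b): quality of life, motor control, balance, cognition, self-assessment, carer diary, smell, microbiome. No adverse events.
- Section 12, outcome measures by visit: body measurements, the same domains plus social cognition, and stool and saliva samples. No adverse events.
- Section 12b: 18 listed tools. None is an adverse-event form. The nearest is the carer diary, described as covering daily activities; its form (Appendix 7) is not visible in the text reviewed, and no section gives it a safety purpose.
- Section 12c: asserts safety from past work only.
- Section 13: no safety analysis.
- Appendix 8: adds screening for falls and cardiac risk before entry, but no recording of events during treatment.

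**2. Is the primary outcome tied to the rest?**
- Aim (Section 3): yes, it names quality of life.
- Objectives (Section 4): no.
- Hypotheses (Section 5): no.
- Instrument, time point, contrast: none under 10a. PDQ-39 is collected but classed under 10b.

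**3. What could 20 treated participants show about harm?** Input: n = 20 in Group 1 (Section 8c). With zero events, the exact upper limit for the proportion affected is:
- one-sided 95%: 1 − 0.05^(1/20) = 0.139, or 13.9%
- two-sided 95%: 1 − 0.025^(1/20) = 0.168, or 16.8%

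The chance of seeing at least one affected participant is 1 − (1 − p)^20. For assumed true rates:
- p = 1%: 18%
- p = 5%: 64%
- p = 10%: 88%

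An effect in 1 in 100 participants would therefore go unseen about 82% of the time.

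**4. What could 20 per arm show on PDQ-39?** Assumptions: two-sided 5% level, no dropout, normal approximation, and a between-group difference of 0.5 SD. The 0.5 SD is a benchmark borrowed from Section 13b, which uses it for individual change.
- Power = Φ(0.5 × √(20/2) − 1.96) = Φ(1.581 − 1.960) = Φ(−0.379) ≈ 35%.
- For 80% power: n per arm = 2 × (1.960 + 0.842)² / 0.5² ≈ 62.8, so 63.
- Difference detectable with 80% power at 20 per arm: 2.802 × √(2/20) ≈ 0.89 SD.

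**The case against.** The strongest reply is that this is a small proof-of-concept study with deliberately basic statistics, meant to inform a larger trial. PDQ-39 is collected, self-assessment is scheduled at each assessment, and Section 13b covers each outcome measure, so quality of life can be analysed. The choice of score and the multiplicity rules may sit in an analysis plan that is not shown. This stands in part, and it rules out several stronger readings that a reader might infer.

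- *That nothing tests the primary question.* This is true of the safety hypothesis only. For quality of life the defect is that PDQ-39 is not designated, not that it is absent.
- *That aim and primary outcome conflict.* They do not: the Section 3 sentence, read to its end, includes quality of life. The outliers are hypothesis 5a and the objectives.
- *That any measure listed under 10b could be promoted to the main result, with a large false-positive rate across all measures and visits.* Item 10a fixes the domain as quality of life, so a motor test as headline would depart from the protocol. Section 13b sets no significance level and does not plan a test of every measure at every visit. The documents give no basis for a family-wise error figure.
- *That harms will certainly go unrecorded.* Ordinary clinical or ethics reporting may capture some events. The protocol simply does not plan it as data for 5a.

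Two limits also apply. The protocol labels PDQ-39 as self-assessment and the content of Appendix 4 is not visible, so treating it as the quality-of-life measure is an inference from the tool list. The text between Sections 6 and 8 was not available for review.

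What the reply does not answer is the first break. An analysis plan can choose a PDQ-39 score, but it cannot analyse adverse events that the protocol never collects.

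**Conclusion.** The point holds as a contradiction within the protocol. Hypothesis 5a has no corresponding outcome, measurement or analysis in any section seen. The primary outcome agrees with the aim but with no hypothesis or numbered objective, and its most plausible instrument is classed as secondary.

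Its size in practical terms: even a perfect safety record in the active arm is compatible with up to 13.9% of such participants being affected (one-sided 95%; 16.8% two-sided). The wording of 5a is therefore unprovable at this sample size, even with full adverse-event collection. The exact limits assume only independent participants and complete follow-up of all 20. The 35% power figure rests on the assumptions listed with it and is a caution about the repair, not a separate fault. The matter should be settled before participants are treated, since missing event data cannot be reconstructed.

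**What to change.** Align the hypothesis, the primary outcome and the measurements. There are two coherent ways to do so.

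1. **Quality of life primary.** This is the smaller change, since Section 3 and item 10a already point there. Name one PDQ-39 score at week 12, active versus sham, as the primary outcome; remove PDQ-39 from 10b; reword 5a and add a matching objective. Week 12 precedes the active treatment that Section 14 offers to the sham group. Report the result as an estimate with a confidence interval, given the limited power.
2. **Safety primary.** If the sponsor prefers to keep 5a as a safety question, make adverse events the primary outcome and move quality of life to a named secondary outcome measured by PDQ-39.

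Under either option:
- Record adverse events at each scheduled treatment session and assessment. Under the home-based contingency, do so at each video assessment, with participant or carer report in between.
- Report the number of participants with at least one event in each arm, with exact 95% confidence intervals.
- Replace the claim of no adverse effects with an estimation statement that gives the upper limit 20 participants can support.

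The cost is a protocol amendment and a short adverse-event form. In the clinic it uses contacts already scheduled; under the contingency it also needs a simple reporting route from home. Option 1 means giving up safety as the leading claim in what Section 1 calls a Phase 1 trial, and the amendment should say why.

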**6. STUDY DESIGN**

Stage 2

Blinded, placebo/sham-controlled trial consisting of 40 participants. Group 1 (20 participants) will be

participants with Parkinson’s disease receiving treatment and Group 2 (20 participants) will be a placebo/sham-control group receiving no treatment. All groups will begin intervention in

August 2021. Treatment will consist of PBMt to the head and nose (either active or

placebo treatment), 3 times per week for 12 weeks. Outcome measures to be collected by Specialist

Examiners and the Physiotherapists.

**8. STUDY POPULATION**

Two groups of participants will be recruited: 20 participants with PD receiving active intervention (Group 1) and 20 participants with PD receiving sham/placebo intervention (Group 2)

**8a. Inclusion criteria**

- Females and males aged 60–85 years
- Diagnosed with Idiopathic PD (by UK Brain Bank Criteria) with Modified Hoehn & Yahr (H&Y) Stage I-III during ON periods
- ≥3weeks of stable anti-Parkinson’s Disease medication.

**8b. Exclusion** **criteria**

Patients will be excluded from the study, if they:

- Are not capable of self-care
- Have a cognitive impairment with Montreal Cognitive Assessment (MOCA) score of <24
- History of significant psychotic episode(s) within the previous 12 months
- History of suicidal ideation or attempted suicide within previous 12 months.
- Take potentially photosensitizing medication, especially imipramine, hypericum, phenothiazine, lithium, chloroquine, hydrochlorothiazide, or tetracycline
- have a history of structural brain disease, active epilepsy, stroke or acute illness, factors affecting gait performance and stance such as severe joint disease, orthopaedic injuries, weakness, peripheral neuropathy with proprioceptive deficits, severe peripheral vascular occlusive disease, severe musculoskeletal disorders, uncorrected vision, vestibular problems or other severe conditions that would:
  - preclude the use of PBM therapy
  - place the patient at risk during evaluation of their PD, or
  - interfere with the evaluation of their PD
- have cardiac disease
- Patients who are currently participating in other trials regarding the treatment of PD, such as advanced therapies (Duodopa, Apomorphine, DBS).

**8c. Sample size**

- Group 1 - 20 participants
- Group 2 - 20 participants

**9. STUDY COHORT**

- Groups 1 participants with PD receiving active intervention.
- Groups 2 participants with PD receiving sham/placebo intervention.

**10. RECRUITMENT STRATEGY**

Potential participants will be recruited from specialised private clinics and neurologists at the Sydney Adventist Hospital through paper advertisements and referrals from specialist clinicians.

**11. STUDY OUTCOMES**

**10a. Primary Outcome:** Improved quality of life

**10b. Secondary Outcomes:**

- Course motor control (up-and-go test; timed walk; step test)
- Fine motor control (spiral test; 9-hole peg test; writing task)
- Balance (static; tandem)
- Cognition (Montreal Cognitive Assessment)
- Self-assessment (PDQ39 questionnaire; PDSS sleep scale)
- Carer diary of daily living
- Smell identification test
- Microbiome analysis

**12. STUDY PROCEDURES**

**11a. Study procedure**

The PBMt intervention will consist of 3 treatment sessions per week for 12 weeks (Groups 1). Participants in the active treatment group will receive transcranial light treatment with a PDNeuro LED helmet device (parameters given in Appendix 1). The treatment areas are 20 points (

154.5 joules total energy). The treatment time is 24 minutes. Participants in the placebo/sham group (Group 2) will receive the same apparent treatment as Group 1, except that they will be “treated” with sham transcranial LED devices that delivers no light.

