The Sydney proof-of-concept trial follows on from proof-of-concept trials which have been completed in Brisbane and Adelaide. The Brisbane trial was a randomised placebo trial using transcranial photobiomodulation and showed significant differences between the treated and placebo group. The Adelaide trial was a waiting-room design with transcranial, intranasal, cervical spine and abdominal photobiomodulation; results are still being analysed but look very encouraging, including potentially positive changes in the microbiome. The Sydney trial will be a case-matched trial and use abdominal and cervical spine photobiomodulation only. The Sydney trial will be conducted over a 12-week treatment period and will assess a number of outcome measures, including motor abilities, cognitive function, microbiome changes, cytokine levels and potential Parkinson’s disease marker changes, as well as self and carer assessments of wellness. The trial is to be conducted in two stages: an initial cohort will be assessed in September, to begin treatment in October. A further cohort will begin treatment in August 2021. The funding for the Sydney trial has been provided by the San Foundation and from private donors. Additional funding ($27,000) has been obtained to conduct the second stage of the trial. The results from all three trials will be used to argue for a large-scale, randomised, double-blinded trial.

The idea for this study emerged after a previous study evaluating the application of photobiomodulation in participants with PD was completed (approved by Griffith University HREC). Ethics approval for this study is being sought through the AHCL HREC. This study will be a simplified blinded placebo/sham-controlled trial with the following sites:

- Northshore Musculoskeletal and Laser Physiotherapy Clinic, [name].
- Photobiomodulation Clinic, Specialist and GP Centre, San Hospital, [name]
- [name], San Hospital, [name]

The sponsor and the supplier of devices for this study will be SYMBYX Biome Pty Ltd, [name]

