**17. CONTINGENCY PLAN**

In the event that the currently proposed protocol is unable to proceed due to uncontrollable and/or unforeseen restrictions or regulations (such as those imposed by government or global bodies e.g., COVID-19 pandemic lockdown restrictions) that directly or indirectly affect:

1. The study site(s).
2. The participant’s ability to participate in the currently proposed study protocol.
3. The researcher’s ability to conduct the currently proposed study protocol.

Several changes constituting a new contingency protocol will be formulated and implemented to adhere to such restrictions/regulations (See Appendix 8.). A layman’s version of the contingency protocol will also be included as part of the PICF and handed to participants as part of the recruitment and consent process, including a separate clause to indicate that participants have received, read, and understood the contingency protocol. Information about recruitment for the study will be advertised on public media platforms, with contact details available for interested potential participants to contact the research team directly.

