**Appendix 1**

PDNeuro (LED) Primary Specifications:

- PDNeuro Helmet LED
- LED positions: Transcranial - 20 LED locations, each containing 1 x infra-red (IR) 810nm LED and 1x red 660nm LED; nasal – 1 x IR 810nm LED.
- Average power output: 660nm LEDs 71.2 mW; 810nm transcranial LEDs 103.4 mW; 810nm nasal LED 20mW.
- Duty cycle: 50% all diodes
- Treatment time: 660nm LEDs 12 minutes; 810nm transcranial LEDs 12 minutes; 810nm nasal LED 24 minutes.
- Total light energy delivered: 660nm LEDs 51.3 joules; 810nm transcranial LEDs 74.4 joules; 810nm nasal LED 28.8 joules; TOTAL = 154.5
- pulse frequency: all diodes 40Hz.

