**Appendix 8**

Contingency protocol

In the event that the currently proposed protocol is unable to proceed due to uncontrollable and/or unforeseen restrictions or regulations, the following changes will be implemented to the existing protocol constituting a new contingency protocol.

1. **Study design**
   1. Treatment will consist of home-based (in the participant’s own home) PBMt to the head and nose (either active or placebo treatment), 6 daily treatments per week for 12 weeks. Outcome measures to be supervised and data collected via the use of video link by Specialist Examiners and the Physiotherapists.
2. **Study setting/location**
3. Study location for both treatment outcome measures assessments will be changed to the participant’s own home.
4. **Inclusion criteria**
5. In addition to the inclusion criteria already stipulated, eligible participants will require:

   - Sufficient space (around 9 m^2^) to be able to perform motor assessments.
6. - Stable and sufficiently fast home-based internet connection for uninterrupted video calls and video conferencing.

   - Knowledge (self or carer) of using a phone and/or tablet applications on either IOS or Android platforms.**Study procedure**
7. In the absence of researcher/specialist-directed intervention, to ensure blinding of participants from group allocations and to reduce the change of participants inadvertently realising that they are in the sham, participants will be informed that there are 3 groups rather than 2 (Group 1: receiving red and infra-red light; Group 2: receiving infra-red light only; Group 3: receiving sham). In fact, there will remain to be 2 groups (Group 1: receiving red and infra-red light; Group 2: receiving sham).
8. **Outcome measures**
9. Outcome measures will be performed at the commencement of the trial before intervention (baseline, week-0), then after 2, 4, 6, 8, 10-weeks of treatment, and at the end of the trial (12-weeks of treatment), and at 6-months (3-months of zero intervention wash out).
10. All outcome measures will be conducted and recorded using a combination of self-reported assessment, visual assessment via video link with a specialist examiner (during live video or pre-recording by the participant).

1. **Consent process**
2. All previous in-person appointments during the consent process will now be conducted via video-link. For example:

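### The sham helmet is dark and the active helmet shows red light, with no masking described, so the arms are likely distinguishable and the subjective outcomes are open to expectancy favouring active treatment

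*Protocol*

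**What the plan says.** **Blinding claim.** Section 2 says: "This study will be a simplified blinded placebo/sham-controlled trial with the following sites". Section 6 says: "Blinded, placebo/sham-controlled trial consisting of 40 participants". Neither states who is blinded.

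**Devices.** Section 11a says sham participants "will receive the same apparent treatment as Group 1", and the same sentence says they are given "sham transcranial LED devices that delivers no light". Appendix 1 describes the active helmet as having 20 locations, "each containing 1 x infra-red (IR) 810nm LED and 1x red 660nm LED". The 660 nm LEDs run for 12 minutes per session.

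**Outcomes.** The primary outcome is quality of life, with no instrument named. The only listed tool of that kind is the PDQ-39, which the secondary outcomes class as self-assessment. Also listed are a sleep scale, a carer diary, timed and balance tests, and microbiome analysis. Section 6 has outcomes collected by specialist examiners and physiotherapists.

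**Contingency.** If treatment moves to the home, Appendix 8 has participants told of three groups (red plus infra-red, infra-red only, sham), although only two exist. The stated purpose is "to ensure blinding of participants from group allocations and to reduce the change of participants inadvertently realising that they are in the sham". Section 17 says that a lay "version of the contingency protocol will also be included as part of the PICF".

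**The concern.** The protocol itself labels the 660 nm LEDs red, as distinct from infra-red, so the active device gives off a visible signal that the sham does not. Section 11a asserts that the two treatments look alike but does not say how 20 red LEDs are hidden. The clinic protocol describes no dummy light, eye cover, shielding or check of blinding.

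What is at stake is the reading of a positive result. Participants who believe they are on active treatment may report better quality of life and sleep and try harder on timed tests. Carers who know the allocation may record more improvement. This bias runs in favour of active treatment, and no analysis can remove it afterwards. Section 2 intends the results to support the case for a large double-blinded trial, so a difference that cannot be told apart from expectancy would weaken that case.

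**Working it through.** **1. The protocol's own figures.** Appendix 1 gives average power and time by LED type. Energy = power × time.

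- 660 nm: 0.0712 W × 720 s = 51.26 J (stated 51.3)
- 810 nm transcranial: 0.1034 W × 720 s = 74.45 J (stated 74.4)
- 810 nm nasal: 0.020 W × 1440 s = 28.80 J (stated 28.8)
- Sum: 154.51 J (stated 154.5)

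The figures reproduce. Red light is 51.3/154.5 = 33% of the stated energy. In clinic there are 3 × 12 = 36 sessions, so 36 × 12 = 432 minutes of red light in the active arm and none in the sham arm.

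**2. What the three-group story can do.**

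| Participant sees | True scheme (2 groups) | Told scheme (3 groups) |
|---|---|---|
| Red light | Active | Red plus infra-red, so active |
| No light | Sham | Infra-red only, or sham |

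The story leaves a sham participant uncertain. Under either scheme, red light identifies active treatment.

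**3. Illustration of size.** The protocol gives 20 per arm but no alpha, standard deviation or correlation. Assumptions: two-sided 5% test, no true effect, and expectancy shifting the active arm by b = 0.2, 0.3 or 0.4 SD.

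*Comparison of means.* Noncentrality = [b/√(1 − r²)] × √(20/2), where r is the correlation of baseline with follow-up. Degrees of freedom are 38 without adjustment (r set to 0) and 37 with it. For example, b = 0.4 and r = 0.5 give 0.4/0.866 × 3.162 = 1.461; against a critical value of 2.026 the rejection rate is 29.6%.

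| Analysis | b = 0.2 | b = 0.3 | b = 0.4 |
|---|---|---|---|
| Unadjusted | 9.5% | 15.2% | 23.4% |
| Baseline-adjusted, r = 0.5 | 11.0% | 18.7% | 29.6% |
| Baseline-adjusted, r = 0.7 | 13.9% | 25.3% | 40.7% |

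*Responder comparison.* Section 13b plans counts of participants improving by more than half a baseline SD, compared by chi-square. It describes comparison between time points; a between-arm version is my adaptation. With normal scores and equal SDs, the probability of response is 1 − Φ[(0.5 − b)/√(2(1 − r))], with b = 0 for sham. At r = 0.5 this is 30.9% on sham and 38.2%, 42.1% and 46.0% on active. Summing exactly over the two binomials gives:

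| Uncorrected chi-square | b = 0.2 | b = 0.3 | b = 0.4 |
|---|---|---|---|
| r = 0.5 | 8.0% | 11.5% | 16.4% |
| r = 0.7 | 9.9% | 15.9% | 24.4% |

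**The case against.** **Distinguishability is inferred.** The protocol does not describe helmet opacity, light leakage or whether carers attend clinic sessions, and it says the treatments look the same. Each participant sees only one device, so a clinic participant who sees red identifies active treatment only if they know or guess that the sham is dark. This stands: *likely distinguishable* is as far as the text goes. A reader might infer that participants, carers and staff can all certainly tell the arms apart, but the documents do not establish that.

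**Role separation.** A reader might also infer that the treating physiotherapists assess their own patients. Section 6 says "Outcome measures to be collected by Specialist" Examiners and the physiotherapists, but the text at hand does not say who delivers the sessions and contains no section 7. Overlap is possible, not shown.

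**Consent form.** Section 17 could lead a reader to conclude that the PICF gives both a two-group and a three-group account. The PICF is not at hand, so this is something to check. If the three-group text does reach every participant, the cover story also extends beyond the home setting.

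**Primary outcome.** That it is self-reported is inferred from the PDQ-39 being the only matching tool, and the PDQ-39 itself is listed as secondary.

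**Magnitude.** The protocol plans no baseline-adjusted comparison of means, so 41% must not be read as the trial's error rate. It is the top of a range set by assumed b and r. A continuity-corrected chi-square would reject in 3.5–8.6% (r = 0.5) or 4.7–13.9% (r = 0.7) of trials, although by the same calculation its rate without bias is only about 2%.

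**Proportion.** This is a proof-of-concept trial whose primary hypothesis concerns adverse effects, and microbiome results are largely insensitive to expectancy. That limits the reach of the problem but does not protect the efficacy outcomes.

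**Conclusion.** The concern holds in a bounded form. The trial is called blinded and the sham is said to look the same, but a dark sham is set against 20 red LEDs and the clinic protocol describes nothing to hide the difference. The arms are likely distinguishable to participants and to staff who see the device running, and to carers if treatment is at home. Appendix 8 shows that the risk was recognised, but its remedy protects one side only.

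Quality of life, sleep, the carer diary and the effort-dependent motor tests are therefore open to expectancy in favour of active treatment. The direction is clear; the size is not established by the documents. Under the assumed bias of 0.2 to 0.4 SD, a nominal 5% error becomes about 10–23% unadjusted, 11–30% or 14–41% with baseline adjustment at r = 0.5 or 0.7, and about 8–24% for the uncorrected responder comparison across those two correlations.

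**What to change.** 1. State who is blinded: participant, carer, treating staff, assessor.
2. Make the devices visually indistinguishable in use. One way is the same opaque eye cover and helmet cover in both arms, fitted before switch-on and removed after switch-off, once confirmed compatible with the device.
3. Have all post-baseline outcomes taken by existing staff who did not treat that participant.
4. Ask participant, carer and assessor to guess the allocation at week 12, before the sham group is offered active treatment (section 14), and report a blinding index by arm.
5. Replace the three-group statement only if the masking also works in the home contingency, where it is at present the only stated protection and covers cannot be supervised in person. Check that the PICF describes the groups consistently.
6. If the light cannot be masked, describe participant blinding as incomplete and interpret the subjective outcomes accordingly.

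The cost is a set of covers, rostering of existing staff, one extra question and a protocol amendment, with a PICF amendment if the check calls for one. The downside for participants is slight discomfort from the covers. The number of participants and the outcome measures do not change.
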